#### Follow-up after occurrence of an adverse event

All adverse events will be observed until their remission or stabilization. Depending on the circumstances, this observation might necessitate evaluation by referral to the patient’s general practitioner and/or specialist.

### Procedures and control

#### Selection of subjects

Patients diagnosed with FXS will be included in a preliminary ‘potential subjects’ group. Before any selection activity is undertaken, a written informed consent form, signed and dated, is to be obtained from each parent or guardian. The patient’s parents will be informed, before any action is taken, of the purposes of the study, and any doubts expressed will be answered. It must be stressed that patients have the unconditional right to withdraw from the study at any time. They will be asked to return to the health-care clinic to begin the study procedure.

#### Study periods

*Entry into the study (t0)*: The child’s parents and/or guardians agree to be included and sign the informed consent to enter into the clinical active phase of the study. The CPRS-R, CTRS-R, WSIC-R and DBC-P24 results will be assessed, taking into account that a score of at least 50 on the CPRS-R is a prerequisite for entry into the study. The baseline blood and urine analyses will be carried out for included patients. The PGWBI for the parents and guardians will be calculated.

*Intermediate period (12 weeks, t1)*: The CPRS-R, CTRS-R, WSIC-R and DBC-P24 scores will be calculated. The t1 blood and urine analyses will be carried out for included patients. The PGWBI scores for the parents and guardians will be calculated.

*End of study period (24 weeks, t2)*: The CPRS-R, CTRS-R, WSIC-R and also DBC-P24 are calculated. The T2 blood and urine analyses will be carried out for patients included in the study. The PGWBI for the parents/guardians will be calculated.

### Data analysis

#### Calculation of statistical power, establishment of sample size and safety

The sample size will be established by means of a pilot scheme based on a phase II effectiveness trial with 30 patients monitored over the course of 6 months for a level of significance of 0.05 and a statistical power of 0.8, taking the least favourable case. On the basis of the prevalence of FXS, 13 patients per group (26 in total) will be needed. This sample size will then be overdimensioned to allow for a possible dropout rate of 10%, and so the minimum sample size is to be calculated as *N* = 30 (15 patients per group).

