**Discussion:**

A limited number of clinical trials have been carried out on children with FXS, but more are necessary as current treatment possibilities are insufficient and often provoke side effects. In the present study, we sought to overcome possible methodological problems by conducting a phase II pilot study in order to calculate the relevant statistical parameters and determine the safety of the proposed treatment. The results will provide evidence to improve hyperactivity control and reduce behavioural and learning problems using ascorbic acid (vitamin C) and α-tocopherol (vitamin E). The study protocol was approved by the Regional Government Committee for Clinical Trials in Andalusia and the Spanish agency for drugs and health products.

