## Background

Fragile X syndrome (FXS) was first described by Martin and Bell in 1943 in families with several males affected by sex-linked mental retardation [1]. It later was identified as the most common cause of inherited mental retardation [2–4]. The prevalence of FXS has been estimated at 1 in 2,500 males and 1 in 4,000 females [5, 6].

In addition to moderate to severe mental retardation, individuals with FXS exhibit macroorchidism—an elongated face, long ears, connective tissue dysplasia, hyperactivity, autistic-like and stereotypical behaviours, speech delay and increased sensory sensitivity [7, 8]. Neuropathological features of FXS are a long, thin, tortuous appearance of cortical dendritic spines, increased intracranial volume, enlarged ventricles, increased volume of selective subcortical grey-matter regions and decreased size of the posterior cerebellar vermis [9], and, in a mouse model, altered glucose metabolism [10].

The name *fragile X syndrome* came into existence upon the discovery of a fragile site in the long arm of the X chromosome detected by cytogenetic testing in a cell culture medium deprived of folic acid [11]. The fragile X mental retardation 1 (*FMR1*) gene was linked to the region (Xq27.3), and a dynamic CGG repeat expansion mutation was identified as the cause of the syndrome [12]. A full mutation with more than 200 CGG repeats causes methylation of *FMR1* and leads to transcriptional silencing of the gene [13]. It has been established that a normal range of CGG repeats varies between 6 and 55, and a CGG expansion over this range is considered abnormal. An unstable premutation allele consists of more than 55 CGG repeats, resulting in reduced levels of the fragile X mental retardation 1 protein (FMRP) encoded by *FMR1*, despite a larger quantity of its mRNA. This may be due to a compensatory mechanism derived from a translation problem in the premutated mRNA [14]. A late-onset neurodegenerative disorder that causes intention tremor, problems with coordination and balance (cerebellar ataxia) and cognitive disability has been described in males and females older than 50 to 55 years of age who are carriers of a premutation allele. This disorder is known as fragile X premutation tremor/ataxia syndrome, which is caused by an increased level of mRNA that leads to neurotoxicity in the brain [15].

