#### General considerations

A descriptive statistical analysis will be performed using statistics of central trend and dispersion for the quantitative variables and frequency distributions for the categorical variables carried out separately for the experimental and control groups. The baseline variables will be compared using these techniques. A flow diagram will be drawn to show the sequence from the initially eligible population to those excluded from the study (refusals, dropouts, lost to follow-up and so forth) in accordance with the criteria in the CONSORT guidelines.

A comparison will be made of between-group differences in the initial and final measurements for the diverse elements of the CPRS-R, CTRS-R and DBC-P24 using unpaired nonparametric tests. For the final within-group comparison, paired nonparametric tests will be used for nonparametric repeated measures with adjustments for baseline imbalances and scores. The same analysis will be performed for the index of psychological well-being to measure the repercussions of the treatment on family life.

The principal outcome variable (POV) will be taken as the change in global score on the Conners scales, adjusted for the baseline values. A simple linear regression model will be constructed for this POV, and the level of significance will be set at *P* < 0.05. Subsequently, a multiple linear regression model will be created, including the variable ‘Experimental/Control Group’ and adjusting for any baseline variables that may be unbalanced. Statistical adjustment will be performed by means of a multivariate model including the variable group (experimental and control) and concomitant treatment (yes or no). The safety of the treatment will be described in terms of the percentage of adverse effects.

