Two double-blind trials have assessed the safety and efficacy of L-acetylcarnitine (LAC) in boys with FXS and an additional diagnosis of ADHD. Both of the trials were randomized, placebo-controlled studies with a parallel-group design. The first study included 20 patients and compared LAC with a dose of 100 mg/kg/day versus placebo, and the investigators found no significant difference between them based on the WISC-R or the Bender-Gestalt tests and Conners questionnaires completed by teachers. However, the results CPRS-R and CTRS-R questionnaires completed by parents and teachers at school showed a significant reduction (Hedges *g* effect size = −3.94, SE = 0.91) of hyperactive behaviour at the end of the study in the LAC-treated subjects [74]. The second study, classified by the authors as a phase II study, involved eight centres in three European countries. The investigators compared LAC at doses of 20-50 mg/kg/day versus placebo in 63 patients. A statistically significant stronger reduction of hyperactivity and improvement of social behaviour was observed in patients treated with LAC compared with the placebo group, based on the results from the Conners Global Index–Parents (CGI-P) (Hedges *g* effect size = −0.30; SE = 0.28) and the Vineland Adaptive Behaviour Scales Survey Form (Hedges *g* effect size = 0.52 and 0.65, SE = 0.29 and 0.29). They also reported no significant side effects in the LAC group [75].

In one phase II parallel, randomized, double-blind, placebo-controlled clinical trial of 4 weeks’ duration, researchers assessed the efficacy and safety of the ampakine compound CX516 versus placebo in 49 patients with FXS, 27 of whom were taking concomitant psychoactive medication. Twenty-one of the patients had an additional diagnosis of autism, and four had autism spectrum disorder. The results of that study showed no significant improvement in memory, the primary outcome measured, or in secondary measurements of language, attention/executive function, behaviour and overall functioning in CX516-treated subjects compared to placebo. There were minimal side effects, no significant changes in safety parameters and no SAEs [76].

There are also enhanced, abnormal epileptiform discharges consistent with an enhanced rate of clinical seizures in FXS patients, as well as auditory-dependent seizures in the mouse model. There are several studies regarding the use of tocopherol to control seizures in animal models and humans [77].

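### The 80% power claim for 13 patients per group rests on FXS prevalence, which has no bearing on a two-arm comparison of Conners change; under a two-sided t-test it holds only for a difference of about 1.15 SD

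*Protocol article*

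**What the plan says.** The section on statistical power and sample size describes a pilot-based phase II effectiveness trial of 30 patients followed for 6 months, "for a level of significance of 0.05 and a statistical power of 0.8, taking the least favourable case". The next sentence gives the basis: "On the basis of the prevalence of FXS, 13 patients per group (26 in total) will be needed". A 10% dropout allowance then raises the total to 30, or 15 per group.

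The only prevalence figures are in the Background: "The prevalence of FXS has been estimated at 1 in 2,500 males and 1 in 4,000 females".

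Under General considerations, the principal outcome is the change in global Conners score, adjusted for baseline. It is analysed by linear regression, and the multiple regression includes treatment group. Significance is set at P < 0.05, and the article does not say whether the test is one- or two-sided.

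The abstract calls the study a pilot meant to yield the statistical parameters and assess safety. It also says: "The results will provide evidence to improve hyperactivity control and reduce behavioural and learning problems".

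**The concern.** For a randomised comparison of a continuous outcome, the number per group follows from the significance level, the power, the difference to be detected and the SD. Prevalence affects how hard recruitment is. It does not enter the power of the comparison. The article names prevalence as the reason for 13 per group, so what it states is wrong rather than merely abbreviated. The phrase about the least favourable case does not help: by convention it belongs to a proportion set at 0.5, and this outcome is not a proportion.

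At stake is how the result is read. A trial described as having 80% power invites the reader to treat a non-significant result as evidence against benefit. That reading is fair only for effects as large as those the trial can detect, and the article does not say how large they are. The abstract's promise of evidence on hyperactivity control leans on the same unsupported power.

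**Working it through.** **Inputs from the article:** level 0.05; power 0.80; 13 per group before dropout; 10% dropout; 1:1 allocation; prevalence in males 1/2,500 = 0.0004; continuous outcome compared between two groups. **Assumptions:** two-sided test; for the main figures, an unadjusted t-test, with SD meaning the SD of the analysed outcome.

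**1. The plan's own figures.**
- Dropout: 13/0.9 = 14.4, rounded up to 15 per group, 30 in total (equivalently 26/0.9 = 28.9, made up to 30). This reproduces.
- The 13 per group does not reproduce, because level, power and prevalence do not determine N for a difference in means. Forcing prevalence into other formulas needs an input that the article does not give:
  - Two proportions, 0.0004 against an invented 0.4: 15 per group (12 one-sided). Against an invented 0.5: 11 (9 one-sided).
  - Precision of a single proportion, 1.96² × 0.0004 × 0.9996 / w²: 15.4 for w = 0.01 and 3.8 for w = 0.02.
  - Least favourable proportion, 0.5 against an invented 0.05: 15 per group (12 one-sided). Against 0.10: 20 (16 one-sided).
- Some of these fall near 13, but only through the choice of the invented input, and none describes the principal outcome.

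**2. What 13 per group can detect.**
- Normal approximation: n = 2(1.960 + 0.842)²/d² = 15.70/d². With n = 13, d = √(15.70/13) = 1.10.
- Exact noncentral t with 24 degrees of freedom and noncentrality d√(13/2): 80% power at d = 1.145. At d = 1.15 the power is 80.3%.
- One-sided 0.05, exact t: d = 1.00.
- All 15 per group retained, two-sided: d = 1.06.
- Crediting baseline adjustment, d = 1.145 × √(1 − r²) in raw-score SD, for assumed baseline correlations r: 1.09 (r = 0.3), 0.99 (r = 0.5), 0.82 (r = 0.7).

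**3. Power at fixed differences (t-test, 0.05).**

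| Difference (SD) | 13 per group, two-sided | 13 per group, one-sided | 15 per group, two-sided |
|---|---|---|---|
| 0.30 | 11% | 18% | 12% |
| 0.50 | 23% | 34% | 26% |
| 0.80 | 50% | 63% | 56% |
| 1.00 | 69% | 80% | 75% |
| 1.15 | 80% | 89% | 86% |

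With baseline adjustment at r = 0.3 to 0.7, two-sided power at a raw difference of 0.30 SD is 12% to 18%.

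**4. Expected precision.** The 95% CI half-width at 13 per group is 2.064 × √(2/13) = 0.81 SD, before baseline adjustment.

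**5. Effects cited in the article's Discussion.** Two L-acetylcarnitine trials are given with Conners effect sizes: g = −0.30 (SE 0.28; 63 patients) and g = −3.94 (SE 0.91; 20 patients). With 13 per group, power is about 11% at the first and nearly 100% at the second.

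**The case against.** The strongest reply is that this is a pilot, and a pilot's size may rest on feasibility or precision. The abstract says as much, and in a rare disease 30 boys may be what can be recruited. That supports keeping N = 30. It does not support the sentence claiming 80% power, which the sample-size section makes all the same.

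A second reply is that a journal article condenses the full protocol, so an unstated difference or SD is no fault in itself. That is right, and the omission is not the point here. The point is that the article does state a basis, and the basis is wrong.

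A third reply is that 1.15 SD depends on choices the article leaves open. This also stands. Sidedness is not given, and the planned analysis adjusts for baseline, so the figure could be 1.00 SD or, in raw-score units, about 0.8 to 1.1. Every variant is still a large effect.

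Three stronger readings are tempting but not supported:
- A reader might infer that the trial is powered at only 11% for the effect its own literature suggests. The article cites two very different Conners effects, both for another compound, and adopts neither as its target.
- A reader might recalculate the detectable difference for a rank test. The nonparametric tests are assigned to the separate elements of the scales; the principal outcome is analysed by linear regression.
- A reader might divide 0.30 by 0.28 and conclude that the 63-patient trial was wrongly called significant. That trial may have used a different test, its report is not available here, and nothing in this trial's sample size depends on it.

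**Conclusion.** The point holds. Prevalence cannot justify 13 per group or 80% power, so the claim is unsupported as written. The defect lies in the stated rationale: the one arithmetic step that can be checked, the dropout allowance, is correct.

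As for size, the power figure is true only if the real difference is about 1.15 SD or more (two-sided 0.05, unadjusted). At a moderate difference of 0.50 SD the power is 23%. With an expected half-width of 0.81 SD, a null estimate could not rule out a moderate benefit. The invalidity of the prevalence basis needs none of these assumptions; the sizes rest on two-sided testing and no credit for baseline adjustment, with the alternatives shown above.

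A reader might go further and conclude that 30 patients are too few and the trial should be enlarged. The documents do not support that: they fix no target effect, and the pilot aim is compatible with this size.

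**What to change.** Keep N = 30. In the sample-size section, delete the clause that makes prevalence the basis and the phrase about the least favourable case. Then do one of two things:

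- State the difference and SD actually assumed, with the sidedness of the test, and show that they give 13 per group; or
- Replace the power claim with: *Thirteen evaluable patients per group give 80% power (two-sided 0.05, before baseline adjustment) for a standardised difference of about 1.15; the expected 95% CI half-width is about 0.8 SD.*

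In either case, add that a non-significant result is not evidence of no effect, and soften the abstract's sentence about providing evidence so that it matches the pilot purpose.

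The cost is rewording and a less favourable stated power. No patient numbers, allocation or analyses change.

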#### General considerations

A descriptive statistical analysis will be performed using statistics of central trend and dispersion for the quantitative variables and frequency distributions for the categorical variables carried out separately for the experimental and control groups. The baseline variables will be compared using these techniques. A flow diagram will be drawn to show the sequence from the initially eligible population to those excluded from the study (refusals, dropouts, lost to follow-up and so forth) in accordance with the criteria in the CONSORT guidelines.

A comparison will be made of between-group differences in the initial and final measurements for the diverse elements of the CPRS-R, CTRS-R and DBC-P24 using unpaired nonparametric tests. For the final within-group comparison, paired nonparametric tests will be used for nonparametric repeated measures with adjustments for baseline imbalances and scores. The same analysis will be performed for the index of psychological well-being to measure the repercussions of the treatment on family life.

The principal outcome variable (POV) will be taken as the change in global score on the Conners scales, adjusted for the baseline values. A simple linear regression model will be constructed for this POV, and the level of significance will be set at *P* < 0.05. Subsequently, a multiple linear regression model will be created, including the variable ‘Experimental/Control Group’ and adjusting for any baseline variables that may be unbalanced. Statistical adjustment will be performed by means of a multivariate model including the variable group (experimental and control) and concomitant treatment (yes or no). The safety of the treatment will be described in terms of the percentage of adverse effects.

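### The principal Conners outcome is defined as baseline-adjusted, but no stated model fixes the baseline score as a covariate, later covariates follow chance imbalance, and no model is named as deciding

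*Protocol article*

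**What the plan says.** All of this is in the protocol article, Data analysis, General considerations, unless noted.

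- The principal outcome variable (POV) is the change in the global Conners score, with adjustment for baseline.
- First model: "A simple linear regression model will be constructed for this POV". The 0.05 significance threshold is set in the same sentence.
- Next comes a multiple linear regression with the group variable, "adjusting for any baseline variables that may be unbalanced". The text gives no candidate list and no criterion for imbalance.
- A further sentence says that adjustment will use a multivariate model that includes group and concomitant treatment (yes/no).
- An earlier paragraph plans unpaired nonparametric tests for the various elements of the parent and teacher Conners scales and the DBC-P24.
- On baseline data: "The baseline variables will be compared using these techniques". The techniques meant are the descriptive statistics of the preceding sentence.

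The section on randomization, blinding and assignment, and the legend of Figure 2, give the stratification factors as age and concomitant medication.

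**The concern.** The definition of the outcome and the models offered for it do not fit together. The definition calls for baseline adjustment, but a simple regression has one predictor, so it can hold group or baseline score and not both. The models that do adjust either take their covariates from the observed data or name only group and concomitant treatment. No model fixes the baseline Conners score, usually the strongest predictor of the outcome, and no model fixes age, although the randomization is stratified by it.

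Under randomization, a baseline imbalance is chance. How large it happens to be says nothing about whether the variable predicts the outcome. A rule driven by imbalance can therefore add uninformative covariates, leave out informative ones, and make the model depend on the data. Because no regression is named as the deciding one, the headline p-value is not tied to a single analysis. Both precision and a clear error rate matter in a trial planned around 26 evaluable boys.

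**Working it through.** **The plan's own figure.** The section on power and sample size gives a "level of significance of 0.05 and a statistical power of 0.8" and states that "13 patients per group (26 in total) will be needed". The dropout step reproduces: 13/0.9 = 14.4, rounded up to 15 per group, 30 in total. The 13 itself cannot be reproduced, because no effect size or SD is given; the stated basis is "On the basis of the prevalence of FXS". Solving backwards (two-sided test assumed, normal approximation), 13 per group implies a standardized effect of (1.960 + 0.842) × √(2/13) = 1.10. Below, 13 is used as the evaluable number per arm.

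**Assumptions not in the documents.** Normal scores; baseline–final correlation r of 0.3 to 0.7; six further baseline covariates of modest prognostic value; unbalanced taken as either baseline p < 0.10 or standardized difference > 0.25, with the baseline score among the candidates.

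**Type I error.** Simulation under no effect, 4,000 trials per row, % with p < 0.05:

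| r | Imbalance rule | Simple | Imbalance-selected | Group + concomitant | Any of the three | Fixed baseline model |
|---|---|---|---|---|---|---|
| 0.3 | p < 0.10 | 5.0 | 4.0 | 5.2 | 6.8 | 4.8 |
| 0.3 | diff > 0.25 | 4.9 | 3.7 | 5.2 | 8.1 | 4.8 |
| 0.5 | p < 0.10 | 5.0 | 3.8 | 5.1 | 6.8 | 5.6 |
| 0.5 | diff > 0.25 | 5.5 | 4.6 | 5.4 | 8.9 | 5.6 |
| 0.7 | p < 0.10 | 4.3 | 3.6 | 4.8 | 6.3 | 4.4 |
| 0.7 | diff > 0.25 | 5.0 | 4.1 | 4.8 | 8.0 | 4.9 |

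Each regression alone is near or below 5%. The union of the three is 6.3–8.9%. This is well under the independence bound of 1 − 0.95³ = 14.3%, because the models are highly correlated. With the baseline score put into all three regressions (8,000 trials per setting), the union is 6.5–8.5%.

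**Precision, if the simple regression is run on change without baseline.** With equal variances at both times, scaled to 1:

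- variance of change = 2(1 − r)
- residual variance with baseline in the model = 1 − r²
- ratio = 2(1 − r)/[(1 − r)(1 + r)] = 2/(1 + r)

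| r | Variance ratio | Total N to match 26 with baseline adjusted | Power of baseline-adjusted model if unadjusted change has 80% |
|---|---|---|---|
| 0.3 | 1.54 | 40.0 | 94% |
| 0.5 | 1.33 | 34.7 | 90% |
| 0.7 | 1.18 | 30.6 | 86% |

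**Power of the imbalance rule** (p < 0.10 version, 3,000 trials, effect in SDs of the score):

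| r | Effect | Simple | Imbalance-selected | Fixed baseline model |
|---|---|---|---|---|
| 0.3 | 1.1 | 63.1% | 59.8% | 78.5% |
| 0.5 | 1.1 | 78.2% | 74.1% | 86.5% |
| 0.7 | 0.8 | 70.6% | 67.4% | 75.9% |

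In these settings the imbalance-selected model has less power than even the unadjusted one.

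**The case against.** **Baseline adjustment is plainly intended.** This stands. The word simple may be loose, or the adjustment might be built into the outcome before group is fitted. But no such step is described and no listed model names the baseline score. The precision loss is therefore conditional, not certain.

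**There is an order.** The threshold is attached to the first model and the multiple regression comes after it, so the simple regression could be read as primary. On that reading, the deciding model conflicts with the definition of the outcome.

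**The last two models may be one.** The multivariate sentence may only explain how the adjustment is done, and its list is introduced as inclusive, not exhaustive. A reader might infer that this model excludes the baseline score; the text does not say so, only that the score is not named. With two regressions instead of three, the 6–9% would probably be lower; that case was not simulated.

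**The analysis plan may settle this.** A covariate list could be left to an analysis plan that is not shown. The article, however, states a rule, and the rule is the problem. The trial is also described as a phase II pilot, which lowers the stakes but does not remove the conflict.

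**Stronger readings that the document does not support:**

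- *That choosing covariates by imbalance breaks the 5% level.* Under a fixed rule it is slightly conservative, at 3.6–4.6%.
- *That the rank tests are a further competing analysis of the principal outcome.* Adding them raises the union to 10.4–12.4%, but they are stated for elements of the scales and not for the global score.
- *That baseline variables will be significance-tested under the sentence on comparing them.* That sentence refers to descriptive statistics.

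**Conclusion.** The point holds as a specification fault of moderate size. The model carrying the threshold does not match the baseline-adjusted outcome, the adjusted modelling follows chance imbalance, and none of the models is designated as deciding or names the baseline Conners score or age stratum as fixed.

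The error-rate consequence is about 6–9% in place of 5%, and arises only if any of the three regressions may be called positive. The precision consequence is a variance 1.18 to 1.54 times that of the baseline-adjusted model, and applies only if the simple regression omits baseline. Both rest on 13 evaluable per arm and an assumed correlation of 0.3–0.7; the simulated figures also depend on the assumed covariates and definitions of imbalance. A single fixed baseline model gave 4.4–5.6%, nominal within simulation error. The trial is not invalidated, but the plan should be corrected.

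**What to change.** Designate one primary analysis: a linear model of the 24-week change in the Conners global score on treatment group, baseline value of the same score, age stratum and concomitant medication, tested at two-sided 0.05 and reported as an estimate with a 95% confidence interval. Because the outcome is worded over the Conners scales in the plural, identify which score enters the model.

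Delete the rule that adjusts for whatever proves unbalanced. Keep the descriptive baseline comparison as it is. Label the simple regression, and any other model or rank test, as sensitivity or exploratory.

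The cost is a few degrees of freedom and a change of wording, made before unblinding. No extra patients or data are needed.

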## Methods/Design

We designed a clinical trial to evaluate the effects of an antioxidant combination of ascorbic acid and α-tocopherol on the clinical condition of patients with FXS. The study includes patients from age 6 years up to age 18 with diagnosed FXS. This age limit was chosen because it is within this age range that a decline in hyperactivity and behavioural symptoms may occur. The minimum duration of treatment and follow-up for these patients is to be 6 months. The symptoms most easily measured are the presence and severity of behavioural abnormalities.

Here we present a new therapeutic approach to FXS that is based on the hypothesis that an increase in free radical production and a deficit in vitamins are involved in the pathology and that this often provokes severe comorbidity. Moreover, we take into account that current treatment protocols are frequently ineffective among young children and carry a risk for important potential side effects. Thus, we propose the following goals. (1) Our main goal is to test whether the combination of 10 mg/kg/day α-tocopherol and 10 mg/kg/day ascorbic acid reduces hyperactivity and behaviour abnormalities, improving cognition among patients between 6 and 18 years of age compared to placebo treatment. (2) Secondary goals are to assess the safety of the treatment, in terms of adverse events; to describe metabolic changes resulting from the treatment, as revealed by blood test results; and to measure the impact of this treatment on the quality of family and social life.

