#### Randomization criteria

Criteria set out above (age, diagnosis, consent).Current pharmacological treatment for behavioural symptoms.No contraindications due to the exclusion criteria.

Patients who fulfil these criteria will be included, randomly, in one of the two groups.

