#### Randomization, blinding and assignment to treatment group

Randomization is centralized and performed immediately after the inclusion of an eligible patient. A software program will be used to ensure that allocation concealment is maintained within the pharmacy department at the Virgen de las Nieves Hospital (Granada). The randomization code will be kept concealed by the pharmacy department responsible for dispensing the corresponding medication. Randomization by blocks and stratification for confusion factors (age and concomitant medication) was performed to reduce bias (see Figure 2). Randomization to either the treatment group or the placebo group will be performed only when a patient with FXS is considered eligible to receive the medication included in this study and an informed consent form is signed by the caregiver.

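### Randomisation is stratified by age and concomitant medication, but the adjusted model names only concomitant treatment, so any precision that age offers is left to an observed-imbalance rule

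*Protocol article*

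**What the plan says.** Under Randomization, blinding and assignment to treatment group, the protocol article states: "Randomization by blocks and stratification for confusion factors (age and concomitant medication) was performed to reduce bias". The caption of Figure 2 repeats both factors. The figure itself is not shown, so the age bands and block size are unknown here.

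Under General considerations (Data analysis), the primary outcome is defined: "The principal outcome variable (POV) will be taken as the change in global score on the Conners scales, adjusted for the baseline values". Three regression steps follow:

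- a simple linear regression, to which the 0.05 level is attached;
- a multiple regression with the group variable, "adjusting for any baseline variables that may be unbalanced";
- an adjusted model: "Statistical adjustment will be performed by means of a multivariate model including the variable group (experimental and control) and concomitant treatment (yes or no".

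Age is named in none of them.

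The Methods/Design section links age to symptoms: "This age limit was chosen because it is within this age range that a decline in hyperactivity and behavioural symptoms may occur".

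Under Randomization criteria, the list of conditions that patients meet before being randomised includes "Current pharmacological treatment for behavioural symptoms".

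**The concern.** Forcing balance on a prognostic factor makes the treatment estimate more precise. The reported standard error shows that gain only if the factor is also in the model. Otherwise the variation due to the factor stays in the residual, and the test rejects less often than its nominal level.

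Here one of the two stratification factors is carried into the adjusted model and the other is dropped without a reason. The imbalance rule does not fill the gap. It depends on the data, and it would admit age mainly when stratification had failed.

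The stake is precision in a trial of 13 to 15 boys per arm. Bias and excess false positives are not at issue.

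A smaller wording conflict concerns the other factor. The Randomization criteria section presents current drug treatment as something patients fulfil. The randomisation and analysis sections treat concomitant medication as a factor that varies between patients.

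**Working it through.** **The plan's own figures.** Inflating 13 per group for 10% dropout gives 13/(1 − 0.10) = 14.4, rounded up to 15, so N = 30 as stated. The 13 cannot be reproduced, because no effect size or SD is given. With two-sided 0.05 (sidedness assumed) and power 0.80, it corresponds to a standardised difference of about 1.10 to 1.14 by the normal approximation, or 1.145 by the t-test. That range is used only to set a scale for power.

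**Which age effect matters.** The outcome is a change score adjusted for baseline. The relevant quantity is R², the share of variance in the baseline-adjusted change that age explains. The document gives no value, so a range is assumed.

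**Formula.** With age balanced between arms, the standard error without age divided by the standard error with age is about 1/√(1 − R²):

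- R² = 0.10: 1/√0.90 = 1.054
- R² = 0.20: 1/√0.80 = 1.118
- R² = 0.30: 1/√0.70 = 1.195

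The overstatement is therefore about 5%, 12% and 20%.

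**Type I error.** Take N = 28 (between 26 and 30) and a model with intercept, group, medication and baseline, which leaves 24 degrees of freedom and a critical value of 2.064. Omitting age raises the effective critical value to 2.064 × 1.054 = 2.175, 2.064 × 1.118 = 2.307 and 2.064 × 1.195 = 2.467. The two-sided tail areas are about 4.0%, 3.0% and 2.1%.

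**Simulation with a baseline term, age acting on the change.** Assumptions: N = 28, two age by two medication strata, blocks of 4, baseline-to-final correlation 0.6, a true difference of 1.1 SD of the baseline-adjusted outcome, and 6,000 trials per setting.

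| Age R² | Fall in SE when age is added | Type I error without / with age | Power without / with age |
|---|---|---|---|
| 0 | −0.3% | 5.2% / 5.3% | 77.6% / 77.0% |
| 0.10 | 4.9% | 4.0% / 5.1% | 79.2% / 82.1% |
| 0.20 | 10.6% | 3.6% / 5.7% | 79.1% / 85.7% |
| 0.30 | 16.6% | 2.2% / 5.2% | 80.8% / 90.1% |

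Falls of 4.9%, 10.6% and 16.6% are the same as overstatements of 1/0.951, 1/0.894 and 1/0.834, that is 5%, 12% and 20%. The average estimate stayed within 0.005 of zero under the null. The power gaps here are 2.9, 6.6 and 9.3 points, in line with a working range of about 2, 5 to 6 and 9 to 10. A separate simulation without a baseline term (N = 30, difference 1.145) gave smaller gaps, 2.1, 4.1 and 5.5 points, because power there started at about 0.90.

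**Simulation with age acting on symptom level only.** The set-up is the same, but age shifts baseline and final scores equally and baseline is in the model.

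| Baseline-to-final correlation | Fall in SE when age explains 10% / 20% / 30% of level |
|---|---|
| 0.5 | 1.5% / 3.6% / 7.1% |
| 0.7 | 0.5% / 1.7% / 3.1% |
| 0.8 | 0.1% / 0.7% / 1.6% |

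The gain is about 0 to 4% except in the corner that pairs the weakest correlation with the largest age effect. Baseline adjustment absorbs most of a level effect.

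**The case against.** **The size is not in the document.** The protocol article describes symptom level over a 12-year age span. It does not say that the 24-week change differs by age. A reader might infer from "it is within this age range that a decline in hyperactivity and behavioural symptoms may occur" that the standard error is overstated by 12 to 20%. That needs age to explain 20 to 30% of the change after baseline adjustment, which is stated nowhere. This objection stands. The larger figures are conditional, and with no age effect nothing is lost by omitting age.

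**The covariate list may not be exhaustive.** The sentence on the adjusted model says only what the model includes. It leaves out baseline score too, although the outcome definition requires baseline adjustment. This is fair, and it means the text does not exclude age. But the sentence names one stratification factor and not the other, and the only stated route for age is the imbalance rule. It is also unclear which of the three regressions is primary. The simple one, which carries the significance level, names neither factor.

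**Adding age is not free.** The age bands are not visible. Three or more would cost further degrees of freedom at N = 26 to 30. This also stands.

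**The randomisation criteria.** A reader might infer that every patient must be on medication, so that the stratum and the yes/no covariate are constant. The document does not support going that far. The inclusion criteria contain no such requirement, the Figure 2 caption uses the phrase randomisation criteria for the stratification factors, and the model codes treatment as yes or no. Only a wording conflict remains.

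**Conclusion.** The mismatch between the stratified design and the stated model is in the text and holds. Its consequence is conditional. If age predicts the baseline-adjusted change, the estimate remains unbiased, the standard error is too large and the test is conservative.

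The result is modest if age acts on level only. It becomes material, with a power loss of 5 points or more, only if age explains about 20% or more of the baseline-adjusted change. These figures rest on assumed strata, block size, correlations and effect size.

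A reader might take the omission as a source of bias or false positives. The calculations show neither. This is a worthwhile, inexpensive correction and does not threaten the trial's validity.

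**What to change.** In General considerations, prespecify one primary model for the change in Conners score: group, baseline Conners score, age stratum as used at randomisation, and concomitant treatment (yes or no). Age would then no longer depend on the observed-imbalance rule.

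The data are already collected. The cost is one degree of freedom for two age bands and a few for more. If age has no effect, the loss is about 1 power point (0.6 in the simulation above).

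Separately, reconcile the line on current drug treatment under Randomization criteria with the randomisation and analysis sections, which treat it as a yes/no stratification factor and covariate. This is a wording change.
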